## Abstract

**Background:**

Compared to conventional thoracotomy, minimally invasive thoracic surgery (MITS) can reduce postoperative pain, reduce tissue trauma and contribute to better recovery. However, it still causes significant acute postoperative pain. Truncal regional anaesthesia techniques such as paravertebral and erector spinae blocks have shown to contribute to postoperative analgesia after MITS. Satisfactory placement of an ultrasound-guided thoracic paravertebral catheter can be technically challenging compared to an ultrasound-guided erector spinae catheter. However, in MITS, an opportunity arises for directly visualised placement of a paravertebral catheter by the surgeon under thoracoscopic guidance. Alongside with thoracic epidural, a paravertebral block is considered the “gold standard” of thoracic regional analgesic techniques. To the best of our knowledge, there are no randomised controlled trials comparing surgeon-administered paravertebral catheter and anaesthesiologist-assisted erector spinae catheter for MITS in terms of patient-centred outcomes such as quality of recovery.

**Methods:**

This trial will be a prospective, double-blinded randomised controlled trial. A total of 80 eligible patients will be randomly assigned to receive either an anaesthesiologist-assisted ultrasound-guided erector spinae catheter or a surgeon-assisted video-assisted paravertebral catheter, in a 1:1 ratio following induction of general anaesthesia for minimally assisted thoracic surgery. Both groups will receive the same standardised analgesia protocol for both intra- and postoperative periods. The primary outcome is defined as Quality of Recovery (QoR-15) score between the two groups at 24 h postoperative. Secondary outcomes include assessment of chronic persistent surgical pain (CPSP) at 3 months postoperative using the Brief Pain Inventory (BPI) Short Form and Short Form McGill (SF-15) questionnaires, assessment of postoperative pulmonary function, area under the curve for Verbal Rating Score for pain at rest and on deep inspiration versus time over 48 h, total opioid consumption over 48 h, QoR-15 at 48 h, and postoperative complications and morbidity as measured by the Comprehensive Complication Index.

**Discussion:**

Despite surgical advancements in thoracic surgery, severe acute postoperative pain following MITS is still prevailing. This study will provide recommendations about the efficacy of an anaesthesia-administered ultrasound-guided erector spinae catheter or surgeon-administered, video-assisted paravertebral catheter techniques for early quality of recovery following MITS.

**Trial registration:**

ClinicalTrials.govNCT04729712. Registered on 28 January 2021. All items from the World Health Organization Trial Registration Data Set have been included.

## Administrative information

Note: the numbers in curly brackets in this protocol refer to SPIRIT checklist item numbers. The order of the items has been modified to group similar items (see http://www.equator-network.org/reporting-guidelines/spirit-2727-statement-defining-standard-protocol-items-for-clinical-trials/).

## Introduction

### Background and rationale {6a}

Minimally invasive thoracic surgery (MITS) is a surgical method used to perform lung surgery through small incisions between the ribs and includes both video-assisted thoracic surgery (VATS) and robotic-assisted thoracic surgery (RATS) [1]. MITS has increased to almost half of all thoracic surgery in the past decade [2]. Compared to conventional thoracotomy, MITS can reduce postoperative pain, reduce tissue trauma and contribute to better recovery [3, 4]. However, it still causes severe acute postoperative pain [3] and is a risk factor for developing chronic post-surgical pain (CPSP) [5].

Erector spinae plane (ESP) block has emerged as a new regional anaesthesia technique which has had promising early results in attenuating this severe acute pain of MITS. In a recent RCT among MITS patients, single-shot ESP block improved QoR-15 and reduced overall complications at 24 h compared with single-shot serratus anterior plane block [6].

Paravertebral block (PVB) has been widely used for analgesia after thoracic surgery for over two decades, because it reduces postoperative pain and opioid requirements compared with systemic analgesia [7, 8] and, alongside epidural analgesia, is considered the “gold standard” of thoracic regional analgesic techniques [9].

Both ESP and PVB have usually been described as a single-shot technique. This has the advantage of convenience but is limited by the finite duration of analgesia, extending to no more than 12 h at maximum and often considerably less [6, 10]. Catheter techniques offer the prospect of flexibility and prolonged analgesia.

Placement of a thoracic paravertebral catheter can be achieved by an anatomical landmark or ultrasound technique [11]. The ultrasound technique has a higher success rate and safer profile when compared to the landmark technique [12] but is technically challenging. Moreover, despite correct detection of the paravertebral space by ultrasound, the final location of paravertebral catheters can be unknown or problematic and cadaveric studies have revealed that catheters have been misplaced in up to 40% of placements [13, 14].

However, in MITS, an opportunity arises for directly visualised placement of a paravertebral catheter by the surgeon under thoracoscopic guidance [15]. In a meta-analysis [16] comparing paravertebral to epidural analgesia, lower failure rates in paravertebral placement were attributed to the practice of intraoperative surgical placement of the catheter under direct vision. Therefore, insertion of the catheter and verification of its location in the thoracic paravertebral space, by the surgeon under direct vision, could be a more reliable and safe method to guarantee drug delivery to the desired location. However, there are no randomised controlled trials examining the efficacy of this technique to ultrasound-guided paravertebral catheter insertion.

In addition, there are limited clinical effectiveness trials on the catheter-based ESP analgesia technique using patient-centred outcomes. Furthermore, no study has evaluated the effect of acute analgesia over 24–48 h with continuous regional nerve block on chronic persistent surgical pain (CPSP) at 3 months after MITS.

### Objectives {7}

Our main aim and corresponding hypotheses are outlined below.

We will conduct a randomised controlled clinical trial comparing the efficacy of anaesthesiologist-administered, ultrasound-guided ESP catheter analgesia to surgeon-administered, video-assisted PVB catheter analgesia. We will test the hypothesis that anaesthesiologist-administered ultrasound-guided ESP catheter analgesia is equivalent to surgeon-administered, video-assisted PVB catheter analgesia, in terms of early Quality of Recovery (QoR-15) and postoperative respiratory spirometric function at 24–48 h and CPSP at 3 months after MITS surgery.

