### Trial design {8}

This manuscript outlines a research protocol for a double-blind, randomised controlled, equivalence trial. This study is designed as equivalence, as the analgesic effectiveness of a successful paravertebral block is not questioned. Patients that volunteer to participate in this clinical trial will be equally (1:1) and randomly allocated into one of two intervention groups: anaesthesiologist-administered ultrasound-guided erector spinae catheter group (ESP catheter group) or surgeon-administered, video-assisted paravertebral block catheter group (PVB group). Figure 1 illustrates the study flow chart. Recruitment commenced on 12 May 2021, and it is expected to take between 9 and 12 months for completion.

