### Sample size {14}

The established minimum clinically important difference (MCID) in QoR-15 score after surgery is 8.0 [18], and the *SD* of QoR-15 scores is typically between 10 and 16 [range of QoR score is 1–150]. Therefore, we considered a reduction in mean QoR-15 scores by 8 to be clinically meaningful and used this value as our delta (Δ) limit. In addition, we have chosen a standard deviation (*SD*) of 12 to reflect our study population. Based on these assumptions, we considered the following for our sample size analysis. For a two-sided test, assuming a type I error (*α*) = 0.05 and type II error (*β*) = 0.2, a sample size of *n* = 36 per group will have 80% power to detect a statistically significant difference in mean QoR-15 scores.

We aim to enrol *n* = 40 each group to allow for loss to follow-up, missing data or withdrawal of consent. The sample size was estimated using the following formula [19]: *n* = 2*σ*^2^ (*z*1 − *α*/2 + *z*1 − *β*)^2^/Δ^2^, where *α* and *β* are the probabilities of type I and II errors, *σ* is the *SD* and Δ is the delta limit. This calculation was subsequently verified by an online calculator (Georgiev G.Z., “*Sample Size Calculator*”, Available at: https://www.gigacalculator.com/calculators/power-sample-size-calculator.php).

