### Statistical methods

#### Statistical methods for primary and secondary outcomes {20a}

The collected raw data will be initially inspected for any errors; this includes but is not limited to double entry errors, missing data and data that was incorrectly entered. Data will be analysed by GraphPad Prism version 8 (GraphPad, Salt Lake City, UT, USA). The data will be tested for normal distribution according to the Shapiro-Wilk test. Primary and secondary outcomes will be analysed as follows: normally distributed data will be compared between the two groups using the unpaired Student *t* test and non-normal distributed data will be compared by using the Mann-Whitney *U* test. All data will be summarised as mean ± *SD* or median (25–75% range) as appropriate, and *p* value < 0.05 will be considered statistically significant.

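### Equivalence is hypothesised for spirometry and CPSP as well as QoR-15, but only QoR-15 has a limit and the prescribed analysis is a difference test

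*Protocol article*

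**What the plan says.** Objectives {7} says the trial will test whether the ESP catheter is equivalent to the PVB catheter on QoR-15 soon after surgery, and extends the same hypothesis to "postoperative respiratory spirometric function at 24–48 h and CPSP at 3 months after MITS surgery". The equivalence framing is confirmed under Trial design {8}: "This study is designed as equivalence, as the analgesic effectiveness of a successful paravertebral block is not questioned".

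The other sections treat the three outcomes differently:

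- Primary outcome, under Outcomes {12}, is QoR-15 at 24 h alone. Spirometry and CPSP appear under Secondary outcome measures, and Plans for assessment {18a} calls them key secondary outcomes.
- Sample size {14} gives a limit for QoR-15 only: "we considered a reduction in mean QoR-15 scores by 8 to be clinically meaningful and used this value as our delta (Δ) limit". It gives no limit, SD or expected rate for spirometry or CPSP.
- Statistical methods {20a} prescribes one analysis for primary and secondary outcomes: unpaired t test if normally distributed, otherwise Mann-Whitney U, where a p "value < 0.05 will be considered statistically significant". The section on non-adherence and missing data {20c} repeats these tests for the primary outcome. No confidence interval is compared with a limit for any outcome.

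**The concern.** An equivalence hypothesis needs a limit fixed in advance and a rule that compares the estimate and its uncertainty with that limit. Spirometry and CPSP have neither. A difference test can reject equality, but failing to reject it does not show that any remaining difference is small, and in a small sample it often just reflects low precision.

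The Background notes that no study has evaluated the effect of continuous regional block on CPSP after this surgery. The Discussion justifies excluding patients with chronic pain by reference to the 3-month pain results. A statement that the two techniques are equivalent for chronic pain would therefore carry weight, and the plan as written gives it no valid basis.

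**Working it through.** **1. The plan's own figure.** Inputs from Sample size {14}: Δ = 8, SD = 12, two-sided α = 0.05, β = 0.2.

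n = 2σ²(z₀.₉₇₅ + z₀.₈₀)²/Δ² = 2 × 144 × (1.960 + 0.842)²/64 = 35.3, rounded up to 36 per group.

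The stated 36 reproduces; 40 per group are to be enrolled. This is the formula for detecting a difference in QoR-15 and carries no information about spirometry or CPSP.

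**2. The sections side by side.**

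| Outcome | In equivalence hypothesis {7} | Limit {14} | Sample size {14} | Test {20a} |
|---|---|---|---|---|
| QoR-15 | yes | 8 points | 36, enrol 40 | difference, p < 0.05 |
| Spirometry, 24–48 h | yes | none | none | difference, p < 0.05 |
| CPSP, 3 months | yes | none | none | difference, p < 0.05 |

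**3. What 40 per arm could show for a continuous outcome.** Assumptions: true difference zero, no losses, two one-sided tests (TOST), normal approximation. The smallest margin with 80% power, in SD units, is (z₁₋ₐ + z₀.₉₀) × √(2/n), where a is the one-sided level.

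- n = 40, a = 0.05: (1.645 + 1.282) × 0.2236 = 0.65 SD
- n = 40, a = 0.025: (1.960 + 1.282) × 0.2236 = 0.73 SD
- n = 36: 0.69 SD and 0.76 SD respectively

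Power with 40 per arm is 2Φ(margin/√(2/40) − z₁₋ₐ) − 1, set to zero if negative:

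| Margin | a = 0.05 | a = 0.025 | n per arm for 80% (0.05 / 0.025) |
|---|---|---|---|
| 0.4 SD | 12% | 0% | 108 / 132 |
| 0.5 SD | 45% | 22% | 69 / 85 |
| 0.667 SD (the QoR-15 ratio 8/12) | 82% | 69% | 39 / 48 |

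**4. How often the planned test would miss a real difference.** With 40 per arm, a true difference of 0.5 SD is non-significant with probability about 1 − Φ(0.5/0.2236 − 1.96) = 1 − Φ(0.276) = 39%. For 0.33 SD the figure is 68%.

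**5. CPSP, illustration only.** The protocol measures CPSP with BPI and SF-15 scores and defines neither a responder nor a rate. If it were analysed as a proportion with an assumed rate of 20–30% in both arms, the 95% CI half-width for the risk difference is 1.96 × √(2p(1 − p)/n):

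- p = 0.2, n = 40: 1.96 × √0.008 = 17.5 points
- p = 0.3, n = 40: 1.96 × √0.0105 = 20.1 points

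**The case against.** The strongest reply has three parts.

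- **The hierarchy is clear.** QoR-15 at 24 h is the only primary outcome, spirometry and CPSP are secondary, and the lead-in to Objectives {7} speaks of hypotheses in the plural, so one joint hypothesis is not the only reading. This stands, but the point does not depend on a joint reading: both secondary outcomes fall under the word equivalent either way.
- **Margins for secondary outcomes can be left to a statistical analysis plan, which is not shown.** Their absence alone would be no finding. The difficulty lies in what is on the page: the objective states equivalence and {20a} fixes a difference test for the same outcomes. An analysis plan would have to override one of them.
- **The sample may be adequate.** A reader might infer that 40 per arm cannot support equivalence on these outcomes. The document does not allow that conclusion, because it gives no margin or variance for either. At a margin with the same ratio to the SD as QoR-15 (8/12), 40 complete patients per arm have 82% power at one-sided 0.05. What can be said is that no margin or power is justified and that the sample suffices only for wide margins.

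A reader might also infer that the investigators will report a non-significant result as equivalence. The protocol does not say so; {20a} gives no interpretation for p ≥ 0.05. It is only the one apparent route the stated analysis leaves open.

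**Conclusion.** The concern holds in this form: equivalence on spirometry and CPSP is hypothesised without a limit or decision rule, and the prescribed difference test cannot establish it. That follows from the text and needs no assumption.

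The size does rest on assumptions. Forty per arm gives about 80% power at one-sided 0.05 for margins of about 0.65 SD or wider, given zero true difference and no losses; at 0.5 SD power falls to 45%. The CPSP interval of about ±18 to 20 points needs a binary endpoint and a rate that the protocol does not define, so it is illustrative.

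The same mismatch reaches the primary outcome. QoR-15 has a limit, but the tests in {20a} and {20c} do not use it, so narrowing the hypothesis to QoR-15 is not a complete repair unless the decision rule changes too.

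**What to change.** 1. In Objectives {7}, restrict the equivalence hypothesis to QoR-15 at 24 h.
2. In {20a} and {20c}, judge that hypothesis by whether the confidence interval for the between-arm difference in mean QoR-15 lies wholly within ±8, in place of the difference test. State the interval level. At SD 12 and zero true difference, 40 per arm gives 82% power with a 90% interval (one-sided 0.05) and 69% with a 95% interval (one-sided 0.025); with 36 per arm the figures are 76% and 62%.
3. Report spirometry and CPSP as between-arm differences with 95% CIs, and state that no equivalence conclusion will be drawn from p ≥ 0.05.

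If equivalence on either secondary outcome is to be kept, it needs a justified margin, a confidence-interval rule and a power statement.

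The recommended change is one of wording and reporting and needs no additional patients. The cost is that the trial gives up two equivalence claims its stated analysis cannot support.

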### Trial design {8}

This manuscript outlines a research protocol for a double-blind, randomised controlled, equivalence trial. This study is designed as equivalence, as the analgesic effectiveness of a successful paravertebral block is not questioned. Patients that volunteer to participate in this clinical trial will be equally (1:1) and randomly allocated into one of two intervention groups: anaesthesiologist-administered ultrasound-guided erector spinae catheter group (ESP catheter group) or surgeon-administered, video-assisted paravertebral block catheter group (PVB group). Figure 1 illustrates the study flow chart. Recruitment commenced on 12 May 2021, and it is expected to take between 9 and 12 months for completion.

**Fig. 1 Fig1:**
[figure not shown]
Study flow chart

## Methods: participants, interventions and outcomes

### Study setting {9}

The authors aim to conduct a multicentre trial. Ethical approval has been granted for Mater Misericordiae University Hospital (MMUH) and St James’s University Hospital (SJH), Dublin, Ireland, and recruitment has begun. We are currently assessing the suitability and seeking ethical approval for one other potential clinical site in Dublin, Ireland.

### Eligibility criteria {10}

The eligibility criteria for patients to enrol in this study are as follows:

Inclusion criteria:
ASA grade 1 to 4 patientsMale and female age 18–85 yearsUnilateral MITS (VATS and RATS)

Exclusion criteria:
Absence of written consentUnexpected conversion of MITS to open thoracotomyContraindications to peripheral regional anaesthesia block:
Infection at the local siteAllergy to local anaesthesia medicationsPatient refusalPrevious or existing neurological deficitAnticoagulated patientsKnown dementia at time of MITS and inability to give informed consentUnexpected postoperative admission to ICU for continued ventilationExisting chronic pain conditionHistory of opioid abuse

### Who will take informed consent? {26a}

Potential participants for this trial will be identified by a member of the surgical, anaesthetic or research team. A member of the research team will analyse these patient’s electronic medical records to determine if they are potential candidates for this trial, i.e. if they meet the inclusion criteria and have no exclusions.

The suitable patient will be approached the evening before surgery if available. Alternatively, patients will be approached on the ward on the morning of surgery and their suitability to participate in the trial will be confirmed. The purpose of the trial, peripheral nerve blocks (including benefits and risks) and method of follow-up will be explained to the patient. A comprehensive and informative leaflet will be given to each patient, and they will be afforded an adequate amount of time (minimum 10 min) to study it. Participants will be informed that their participation in the study is entirely voluntary and they will have the opportunity to withdraw from the study at any time and this will not affect the quality of care they receive. Subsequently, a member of the research team will obtain informed written consent from the participant.

### Additional consent provisions for collection and use of participant data and biological specimens {26b}

Not applicable. No data and biological specimens will be collected for use in ancillary studies.

### Interventions

#### Explanation for the choice of comparators {6b}

Erector spinae block has been embraced by many anaesthesiologists; however, to the best of our knowledge, there is no clinical effectiveness trial comparing anaesthesiologist-administered, ultrasound-guided erector spinae catheter to surgeon-administered, video-assisted paravertebral block catheter techniques for minimally invasive thoracic surgery in terms of patient-centred outcomes and therefore this clinical trial is warranted.

#### Intervention description {11a}

##### ESP catheter group: anaesthesiologist-administered, ultrasound-guided erector spinae catheter

This peripheral nerve block will be performed or supervised by a consultant anaesthesiologist in regional anaesthesia with experience in the placement of an ESP catheter. The block will be performed as follows: the patient will be positioned in the lateral decubitus position, and the skin will be cleaned with chlorhexidine gluconate 0.5%/isopropyl alcohol 70% solution (ChloraPrep; Becton Dickinson, New Jersey, NJ, USA). A linear ultrasound transducer (SonoSite HFL 50x; SonoSite Inc.) will be placed in a sterile cover. This ultrasound probe will be used to identify the T5 spinous process and the erector spinae muscle group superficial to it. An 18G Tuohy Epidural needle (B. Braun medical) will then be advanced in a cranial-caudal direction. The needle tip will be slowly advanced under ultrasound guidance (in-plane technique) until it is located within the interfascial plane deep to the erector spinae muscle group and superior to the transverse process. Once in position, 10 ml of 0.9% normal saline will be injected to confirm a satisfactory needle position. Following this, 20ml 0.375% levobupivacaine will be injected and then a 20 G Nylon Epidural catheter (Perifix Epidural Catheter, B. Braun medical) will be advanced into this interfascial plane. The catheter will then be attached to a Luer lock connector with an antibacterial filter and secured to the patients back using surgical steri strips and standard dressings. A further bolus of 10ml 0.25% levobupivacaine will be administered via the catheter towards the end of the surgical procedure (> 1 h since the last dose).

##### PVB catheter group: surgeon-administered, video-assisted paravertebral block catheter

This nerve block will be performed or supervised by a consultant thoracic surgeon with experience in the placement of a paravertebral catheter under thoracoscopic guidance. The paravertebral block will be conducted at the start of the surgery after the thoracoscopic ports have been inserted. The block will be performed as follows: A percutaneous puncture point, which is equidistant to the upper and lower intercostal space, 2–3 cm lateral to the midline at the level between T4 and T5 will be marked. An 18 G Tuohy Epidural needle (B. Braun medical) will be advanced perpendicularly through the chest wall at this marked point to lie within the paravertebral space. The thoracoscope will be used to ensure that the epidural needle does not puncture the pleura and then 10–20 ml of 0.9% normal saline will be injected through the epidural needle to confirm a satisfactory position of the needle. This will appear as an induration under the pleura which can be easily seen thoracoscopically. A 20 G Nylon Epidural catheter (Perifix Epidural Catheter, B. Braun medical) will then be advanced into the paravertebral space through the epidural needle. Again, the thoracoscope will be used to ensure that the epidural catheter does not puncture the pleura and lies within the paravertebral space. The catheter will then be attached to a Luer lock connector with an antibacterial filter and secured to the patients back using surgical steri strips and standard dressings. A bolus of 20 ml 0.375% levobupivacaine will then be injected into the paravertebral space by using the catheter.

A further bolus of 10ml 0.25% levobupivacaine will be administered via the catheter towards the end of the surgical procedure (> 1 h since the last dose).

